### Outcome measures

The assessment will focus on three key domains: physical functioning, cognitive performance, and psychosocial well-being. Apart from the following primary and secondary outcomes, demographic and baseline characteristics, like age, height, weight, Body Mass Index, and sex, will be measured.

#### Primary outcomes

The following primary outcomes will be measured to evaluate the efficacy of the intervention program:

##### Physical functioning

The *Short Physical Performance Battery* (SPPB) [45] is a standardized instrument to test the lower extremity functionality (balance, gait speed, leg strength). Participants are required to show a stable stand in an upright position under three conditions (legs closed/feet together, semi-tandem stand, tandem stand). After that, comfortable gait speed will be assessed by measuring the time to walk a 4-m track, starting from a standing position and stopping when the first foot is past the 4-m line. Finally, a five times sit-to-stand transfer will be completed as fast as possible. Each domain is scored between 0 and 4 and SPPB overall scores range from 0 (low mobility/functionality) to 12 (full mobility/functionality). Clinically relevant improvements have been demonstrated to range between 0.99 and 1.34 points for the SPPB [45].

*Gait analysis* (GAITRite: CIR Systems Inc., Clifton, NJ, USA, Optogait: Microgate, Bolzano, Italy, MobilityLab: APDM Inc., Portland, USA, GaitUp: SA, Lausanne, Switzerland or Zebris PDM, Isny, Germany). Gait performance will be assessed by measuring step length, step width, gait speed, and double support phase on a 10-m track, using of one of the mentioned gait analysis systems. Each participant completes three trials: a test trial, one trial at preferred walking speed, and one trial at maximum walking speed. Measured data will be recorded and saved for later analysis by the gait systems software. An accompanying validation study will secure the comparability of the different gait measurement systems.

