#### Assignment of interventions

Assessment and data collection will be done by blinded assessors in a strictly pseudonymized form to guarantee a blinded data analysis.

To avoid performance bias, the measurements and the intervention follow a standardized protocol. All participant information and data will be stored securely and identified by a coded ID number only to maintain the participants’ confidentiality.

To avoid selection bias, a stratified randomization will be conducted to divide the participants into either an intervention group or a waiting time control group. The random allocation will be stratified and executed by lot by the director of the study who will receive the pseudonymized codes of the participants and their baseline characteristics and will not be involved in neither the assessment nor the intervention procedures. Stratification will be based on comparable sex, age, and cognitive performance (according to the Montreal Cognitive Assessment MoCA-Score [44]) to avoid differences in the baseline characteristics of the groups. After assigning the participants to either the intervention or waiting time control group, the pseudonymized participant codes will be sent to the study investigators who are responsible for the data management. The exercise scientist or physiotherapist, who will conduct the intervention, will receive only names of the participants in the intervention group and after 16 weeks names of the waiting time control group without being aware of the control group design.

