### Data collection, management, and analysis

#### Statistical analysis

We will evaluate the effects of the intervention on every quantitative, qualitative, and ordinal outcome, using repeated measures or mixed models, “t” tests, Kruskall-Wallis Mann-Witney tests or the Chi-square tests, depending on the type of outcome and their normal or non-normal distribution. The primary analysis will be a mixed model between-group comparison of the SPPB, gait variables, Serial Sevens, and Verbal Fluency Test, utilising all available data points during follow-up. We will use the Bonferroni correction to appropriately adjust the overall level of significance for multiple comparisons. Between-group differences for all primary and secondary outcomes will be adjusted for baseline values, age, sex, and education. Secondary outcomes will be analysed with similar methodology, using repeated measures mixed model between-group comparisons. All statistical analyses will be performed using SPSS Statistics for Windows (version 25.0, IBM). Statistical significance level is set at *p* < 0.05.

Intention-to-treat analysis will be performed (participants who are randomized into groups after the collection of baseline data). For the intention-to-treat analysis, data of all trial patients in the groups to which they were randomized will be processed, regardless of whether they received or adhered to the allocated intervention. It is assumed that the majority of participants in the two arms will receive the appropriate number of intervention sessions. In addition, a per-protocol analysis of the participants who completed the study without major protocol violation (e.g., who attended more than 80% of the training sessions), will be performed. The per-protocol analysis will be performed as a secondary analysis, if there is a sufficient number of participants in the two arms, who do not receive the intervention protocol or are lost to outcome assessment. Data from those participants, who do not violate the treatment protocols, will be included in the per-protocol analysis. The multiple imputation (MI) technique will be used for dealing with missing data under the assumption that data are missing at random.

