#### Sample size estimate / power calculations

The required sample size was calculated with G*Power (Version 3.1.9.2, Heinrich Heine University of Duesseldorf) [62]. The sample size calculation was approximated with a 2 × 3-factorial analysis of variance (ANOVA) for repeated measures (within-between interaction, small effect size, power of .80 [1-β], 2-sided α-error (95% CI), 2 groups, 3 measurements) based on the primary outcome Short Physical Performance Battery (SPPB). The small effect size used for the calculation of required sample size is based on literature reviews and assumptions of clinically relevant changes for residents in nursing homes with probable cognitive impairment [63]. One hundred eight individuals per region are required in order to detect a clinically meaningful change of ≥1.0 point with a SD of 0.99 points. To account for potential dropouts before study completion, we will inflate the sample size by 30% (20% losses during follow-up; 10% mortality), resulting in a total sample size of 1120 individuals (140 per centre with 70 participants allocated to each group).

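### Primary gait variables come from any of five measurement systems, but the stated adjustment set has no system or centre term: a modest, avoidable loss of precision, not a bias

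*Protocol article*

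**What the plan says.** Under Primary outcomes, Physical functioning, the protocol article lists gait analysis and names the equipment: "GAITRite: CIR Systems Inc., Clifton, NJ, USA, Optogait: Microgate, Bolzano, Italy, MobilityLab: APDM Inc., Portland, USA, GaitUp: SA, Lausanne, Switzerland or Zebris PDM, Isny, Germany". Four parameters (step length, step width, speed and double support) are recorded "using of one of the mentioned gait analysis systems". The section on dual-task cognitive performance records the same four parameters again while the resident performs a cognitive task.

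On agreement between systems, the article has one sentence: "An accompanying validation study will secure the comparability of the different gait measurement systems".

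Under Statistical analysis: "The primary analysis will be a mixed model between-group comparison of the SPPB, gait variables, Serial Sevens, and Verbal Fluency Test". The covariates are then fixed for every outcome: "Between-group differences for all primary and secondary outcomes will be adjusted for baseline values, age, sex, and education". Neither gait system nor centre is among them, and the random part of the mixed model is not described.

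Two further statements bear on the size of the problem. Under Assignment of interventions, the strata do not name centre or system: "Stratification will be based on comparable sex, age, and cognitive performance". Under Sample size estimate / power calculations, the planned numbers are "140 per centre with 70 participants allocated to each group", so the arms are meant to be equal in size within each centre.

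**The concern.** Values from different systems may sit on different levels for the same resident. If so, part of the spread in the pooled gait data is spread between instruments. A model with one baseline slope and no system term cannot separate the two. The slope is then a mixture of the within-system relation, which the adjustment needs, and the between-system relation, which follows the offset one for one. The adjustment becomes less efficient and the offset stays in the residual, so intervals for gait effects are wider than they need be.

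A validation study estimates agreement. Its result cannot be stated in advance, and the article describes no feature of the primary model that would take up an unfavourable one. The variables concerned are the gait and dual-task gait parameters.

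**Working it through.** The article gives no agreement or gait-variance figures, so there is no stated figure to reproduce. Its only calculation concerns the SPPB and does not bear on this point.

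**Inputs from the article.** Five systems, eight centres, 70 residents per arm in each centre (2 × 70 = 140; 8 × 140 = 1120), and the covariate list above.

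**Assumptions.** Each centre keeps one system. Offsets are constant and the same at T1 and T2. Resident variance is 1 at each visit, the between-system offset SD is k (in resident SDs), and the within-system T1–T2 correlation is r. The analysis is reduced to T2 on T1 and arm.

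**Step 1: bias.** Let p_s be the share of residents on system s and d_s its offset. With equal allocation in each centre, p_s is the same in both arms. The mean offset Σ p_s d_s is therefore the same in both arms at T1 and at T2. It cancels from the difference in T2 means and from the difference in baseline means, whatever slope is fitted. The treatment contrast is unbiased.

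**Step 2: baseline slope without a system term.** Slope = (r + k²)/(1 + k²), against r within a system.

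**Step 3: residual variance.** Without a system term it is (1 + k²) − (r + k²)²/(1 + k²). With one it is 1 − r². The ratio simplifies to (1 + r + 2k²)/[(1 + r)(1 + k²)]. Its square root is the ratio of standard errors.

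| k | r | Slope fitted | Residual variance, no system term | With system term | Variance ratio | SE ratio |
|---|---|---|---|---|---|---|
| 0.5 | 0.5 | 0.75/1.25 = 0.60 | 1.25 − 0.45 = 0.800 | 0.750 | 1.067 | 1.033 |
| 0.5 | 0.7 | 0.95/1.25 = 0.76 | 1.25 − 0.722 = 0.528 | 0.510 | 1.035 | 1.017 |
| 1.0 | 0.5 | 1.50/2 = 0.75 | 2 − 1.125 = 0.875 | 0.750 | 1.167 | 1.080 |
| 1.0 | 0.7 | 1.70/2 = 0.85 | 2 − 1.445 = 0.555 | 0.510 | 1.088 | 1.043 |

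**Step 4: simulation check.** The set-up was 8 centres of 108 residents (the article's number per region before inflation for dropout), 1:1 within centre, one assumed system per centre, r = 0.8 and 2000 runs. Without a system term, the mean standard error was 0.0409, 0.0412 and 0.0417 for offset SDs of 0.25, 0.5 and 1.0. With one it was 0.0408. The largest loss is 0.0417/0.0408 = 1.022, about 2%. Mean estimates were close to zero under no effect, and type I error stayed near 5%. This agrees with Step 1, and with Step 3 in that the loss shrinks as r rises.

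**The case against.** The strongest reply is that a journal article condenses the plan. The mixed model may carry a centre effect that is not described, and an agreement limit, a conversion between systems or a same-device rule may stand in a manual or analysis plan. Because allocation is equal within centres, the between-group comparison is protected in any case. Much of this stands. It removes any charge of bias, and it means that the absence of an agreement criterion is not itself a finding. It does not remove the point that the article fixes a covariate set for all outcomes, and that this set could be improved for the gait outcomes at almost no cost.

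A reader might infer more than the text supports:

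- **That residents change system between visits.** This would put the full offset into a resident's change, and into the T3 retention comparison, which has no control arm. Nothing in the article describes such changes. One system per site is the natural reading, and under Assignment of interventions the article says that "the measurements and the intervention follow a standardized protocol". Any figure for this harm would rest on a switching rate with no source in the document.
- **That raw values are pooled whatever the validation study shows.** The article does not say that values enter unconverted. A validation study could yield conversion equations and, though it runs alongside the trial, its result is needed only before analysis.

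**Conclusion.** The point holds as a modest improvement to the stated model. If each centre keeps one system, a constant offset does not bias the treatment effect or inflate type I error. The cost is precision. Residual variance is about 4–7% higher (2–3% in standard error) if the between-system SD is half the resident SD. It is 9–17% higher (4–8% in standard error) in the extreme case where they are equal. Both ranges assume r between 0.5 and 0.7 and offsets that are constant across visits, and the loss is smaller at higher r. The true size is unknown because the article gives no agreement figures.

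The scope is the gait and dual-task gait parameters only. The SPPB walk is timed separately over 4 m. The counts of correct answers and the questionnaires do not depend on a gait system.

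**What to change.** In Statistical analysis, state that the gait and dual-task gait models also include gait system as a fixed effect with a baseline-by-system interaction. Centre can be used instead if each centre uses one system. The main effect recovers the precision calculated above. The interaction allows for baseline slopes that differ between systems. The cost is 4 + 4 = 8 degrees of freedom for five systems, or 7 + 7 = 14 for eight centres, in a trial of 1120 residents. No new measurement is needed.

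Two supporting clarifications belong in the gait analysis paragraph. First, say that each resident is measured on the same system at T1, T2 and T3. Second, say that the validation study will assess comparability, in place of the statement that it will secure it.

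A compulsory change to standardised differences where agreement is poor is not recommended here. It is a matter of preference and would give up natural units.

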##### Dual-task cognitive performance

The *Serial Sevens Test* (SST) [46] aims to assess cognitive functioning. During the SST, participants are being asked to count down from a certain number in steps of seven. Due to the poor cognitive functioning of most participants, a simpler version of the SST will be administered, in which participants have to count down in steps of 3 (S3T) and steps of 1 (S1T). The S3T and S1T will be tested during a single- and dual-task condition (i.e. during gait), in order to evaluate the cost of dual-tasking for cognitive functioning. The number of correct answers within 15 s will be recorded during single- and dual-task conditions as well as the gait parameters step length, step width, gait speed, and double support phase under dual-task conditions with a gait analysis system.

The *Verbal Fluency Test* (VFT) is an additional test for cognitive functioning and part of the MoCA [44]. The VFT is a phonemic fluency test, in which participants are asked to name as many words as possible in a certain time, starting with a specific letter (not allowed are names or numbers). It was shown that verbal fluency is reduced in elderly people with mild cognitive impairments as compared to their non-impaired peers [47]. In accordance to the S3T and S1T, the VFT will be administered during single- and dual-task conditions, to evaluate the cost of dual-tasking for cognitive functioning. The number of correct answers within 15 s will be recorded during single- and dual-task conditions as well as the gait parameters step length, step width, gait speed, and double support phase under dual-task conditions with a gait analysis system.

##### Psychosocial well-being

The short form of the *Health Survey SF12* [48] is a questionnaire, which can be used to examine the health-related quality of life of the participants, who rate their quality of life via twelve items. The items regard eight health concepts which are commonly represented in widely used surveys: (1) physical functioning, (2) role limitations due to physical health problems, (3) bodily pain, (4) general health, (5) vitality (energy/fatigue), (6) social functioning, (7) role limitations due to emotional problems, and (8) mental health (psychological distress and psychological well-being) [49]. The SF12 physical and mental component summary scales are scored using norm-based methods. Both scales are transformed to have a mean of 50 and a standard deviation of 10 in the general U.S. population. All scores above and below 50 are above and below the average [49].

The *Satisfaction with Life Scale* SWLS [49] is a brief instrument with five items to measure global cognitive judgements of satisfaction with one’s life on a seven-point Likert scale. High scores indicate a high satisfaction with life, while low scores indicate a low degree of satisfaction.

#### Secondary outcomes

The following secondary outcomes will be measured to evaluate the efficacy of the intervention program:

##### Physical functioning

The *Barthel Index* [50] is used to systematically record the independence of participants when performing basic ADL via ten items. Feeding, personal toileting, bathing, dressing and undressing, getting on and off a toilet, controlling bladder, controlling bowel, moving from wheelchair to bed and returning, walking on level surface (or propelling a wheelchair if unable to walk) and ascending and descending stairs are rated on a scale from 0 to 15 points depending on the item. Total possible scores range from 0 (totally dependent) to 100 (fully independent) [50].

*Hand Grip Strength* is measured with a hydraulic hand dynamometer (JAMAR, hydraulic hand dynamometer). Three trials with each hand will be executed. Results will also be used to assess the frailty index item weakness.

The *Functional reach* [51] is a clinical measure of balance. It assesses the difference between the arm’s length and maximal forward reach in cm, using a fixed base of support. The test will be executed in a sitting position. The participant sits against the back of a chair next to a wall reaching forward as far as possible without losing balance. Reach distance will be measured with a scale attached to the wall.

For the measurement of *Frailty* this study will apply the original operationalization of the Frailty Phenotype from the Cardiovascular Health Study [52] to enable comparability. A frailty index will be formed out of five measured factors, including an unintentional weight loss of more than 4.5 kg in the past 12 months (shrinking), BMI- and sex-adjusted hand grip strength (weakness), frequency of fatigue in the last week by using two items of the Center of Epidemiological Studies-Depression Scale (CES-D, exhaustion), height- and sex-adjusted gait speed (slowness) and sex-adjusted energy expenditure by physical activity (modified Minnesota Leisure Time Physical Activity Questionnaire).

The short form of the *Falls Efficacy Scale-International* (Short-FES-I) [53] is a seven-item questionnaire with a scoring range between one and four, which provides information on the level of concern about falls for a range of activities of daily living. The number of falls, fall-related injuries and deaths occurring during the 32-week period will be documented by nursing staff.

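### Falls and fall-related injuries are defined as raw counts and assigned to a baseline-adjusted mixed model that does not fit them and uses no time at risk

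*Protocol article*

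**What the plan says.** Under Secondary outcomes, Physical functioning, the article states: "The number of falls, fall-related injuries and deaths occurring during the 32-week period will be documented by nursing staff". It gives no denominator and describes no fall count before the trial.

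The Statistical analysis section lists the methods for all outcomes as "using repeated measures or mixed models, “t” tests, Kruskall-Wallis Mann-Witney tests or the Chi-square tests", to be chosen by outcome type and distribution. For this group of outcomes it is more specific: "Secondary outcomes will be analysed with similar methodology, using repeated measures mixed model between-group comparisons". It also says: "Between-group differences for all primary and secondary outcomes will be adjusted for baseline values, age, sex, and education". The same section plans intention to treat, and multiple imputation under missing at random.

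The Sample size section expects incomplete follow-up: "we will inflate the sample size by 30% (20% losses during follow-up; 10% mortality". The Intervention section says that attendance and reasons for dropping out are recorded; exit dates are not mentioned. The Abstract limits the 32-week test to the intervention group. Assignment of interventions says that the trainer receives the names of the waiting controls after 16 weeks.

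**The concern.** The stated rule and the outcome do not match. A repeated-measures model adjusted for a baseline value needs the variable to be measured at baseline and again later. Falls here are counted only inside the trial window, and deaths cannot have a baseline value at all. No listed method is described as allowing for how long each resident could be observed. A resident who dies or moves out in week 4 without a fall would therefore carry the same zero as one observed to the end.

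If observed time differs between arms, a comparison of raw counts mixes who fell with who stayed. This deserves care because falls and fall-related injuries are the only non-fatal harm-type events that the article names for counting. The Monitoring section sets up no data monitoring committee because it expects no adverse events.

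**Working it through.** **Inputs from the article.** Pooled loss is 20% + 10% = 30%. The size before inflation is 108 per region, with eight regions and 1:1 allocation. The window is 32 weeks, and controls are handed to the trainer after week 16.

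**Assumed, not in the article.** Arm-specific loss; exits uniform over the window; counting that stops at exit; the same true fall rate in both arms. For the illustrations: 1.5 to 2.0 falls per person-year and gamma-Poisson counts with dispersion 1.

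**1. The plan's own figure.** "One hundred eight individuals per region are required in order to detect a clinically meaningful change of ≥1.0 point with a SD of 0.99 points", then "resulting in a total sample size of 1120 individuals (140 per centre with 70 participants allocated to each group". 108 × 1.30 = 140.4, taken as 140 per centre. 8 × 140 = 1120, or 560 per arm. The figure reproduces, and it shows that the 30% is one allowance, not split by arm.

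**2. Expected count ratio under no effect.** With loss L spread evenly, the mean share of the window observed is 1 − L/2. The ratio is (1 − L₁/2)/(1 − L₂/2), with arm 1 losing more.

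| Loss, arm 1 v arm 2 | Mean share observed | Count ratio |
|---|---|---|
| 30% v 30% | 0.85 v 0.85 | 1.00 |
| 35% v 25% | 0.825 v 0.875 | 0.94 |
| 40% v 20% | 0.80 v 0.90 | 0.89 |
| Weeks 0–16, half of 35% v 25%: 17.5% v 12.5% | 0.9125 v 0.9375 | 0.97 |
| Weeks 0–16, half of 40% v 20%: 20% v 10% | 0.90 v 0.95 | 0.95 |

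With exponential instead of uniform exit, the 40% v 20% ratio over 32 weeks is 0.87.

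**3. The same case in events.** Full follow-up gives 560 × 32/52 = 344.6 person-years per arm. At 40% v 20% this becomes 276 v 310. At 1.5 falls per person-year the arms show 414 v 465 falls, a ratio of 0.89. Dividing by person-time gives 1.5 in both arms, a ratio of 1.00. A true rate ratio of 1.10 would appear as 1.10 × 0.889 = 0.98.

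**4. Effect on tests.** Simulated over 32 weeks with 560 per arm and 1500 runs, nominal level 5%:

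| Loss | t test on counts | Mann-Whitney | Rate-ratio test |
|---|---|---|---|
| 30% v 30% | about 5% | about 5% | about 5% |
| 35% v 25% | 9–10% | 10–11% | about 4% |
| 40% v 20% | 24–25% | 27–32% | 5–6% |

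**5. The missing earlier count.** Under randomisation this causes no bias. If prior and later falls correlate at 0.3 to 0.5 (assumed), adjustment would remove r² = 0.09 to 0.25 of the variance.

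**6. The window.** Suppose a true rate ratio of 0.80 during training, with controls trained in weeks 16–32. The control arm's average relative rate is then (1 + 0.80)/2 = 0.90. Over 32 weeks the ratio is 0.80/0.90 = 0.89 if the effect persists in the intervention arm, and 0.90/0.90 = 1.00 if it ends with training. A 32-week total therefore blurs the randomised contrast even when loss is equal.

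**The case against.** The strongest reply is that this is a condensed article. It says what nursing staff document and does not rule out dates. A count model with an offset could sit in a fuller protocol or analysis plan, and a mixed model chosen by outcome type does not exclude one. That stands as far as it goes: time at risk is absent from what is stated here, not shown to be absent from the trial. The Table 2 schedule was also unavailable for this check. But the article does state a rule for all secondary outcomes, and that rule cannot be carried out for these as described.

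Second, the unequal losses are assumed. This stands in full. A reader might infer that 30% planned loss by itself makes the arm with more exits look safer. The article predicts no difference between arms, and equal loss gives a ratio of 1.00.

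Third, nursing staff record falls in the home, so a resident who stops only training or testing may still be counted. This also stands and shrinks the figures. Death, moving out and hospital stays still remove time at risk.

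Fourth, the baseline sentence is generic, and age, sex and education remain usable. True, but the sentence covers all outcomes and should carry an exception.

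Fifth, multiple imputation is planned. It does not repair this sensibly: either a shortened count is taken as complete, or falls are imputed for time after death or departure.

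**Conclusion.** The point holds as a mismatch between outcome and analysis rule, with a conditional risk of bias. The stated baseline-adjusted, repeated-measures rule does not fit falls, fall-related injuries or deaths, and no named method uses time at risk although substantial loss is planned for.

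The size depends on loss differing between arms, on uniform exits and on counting that stops at exit. Under no true effect the count ratio is then 0.94 to 0.89 over 32 weeks for differences of 10 to 20 percentage points. It is about 0.97 to 0.95 over weeks 0–16 if half the loss has occurred by then. With equal loss there is no distortion.

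Two wider readings are not supported. The argument does not carry over generally to deaths: an arm that loses more residents by death shows more deaths, not fewer. And the missing pre-trial fall count costs precision and blocks the stated adjustment, but does not create the bias.

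**What to change.** - Have nursing staff record the date of each fall and fall-related injury, and the dates of death, moving out and hospital absence.
- Compare falls and injuries as rates per resident-day, for example by negative binomial regression with log days observed as offset. Analyse deaths as time to event.
- State that these outcomes are exempt from the general mixed-model and baseline-value rule.
- Confine the randomised comparison to weeks 0–16, because the waiting controls pass to the trainer after that. Report later events descriptively.
- Optionally, take a look-back fall count from the nursing documentation already consulted for eligibility and use it as a covariate for precision.

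The cost is a date column, some file abstraction (more if the look-back is added) and a sentence of analysis text. The dates should be settled before data collection, since they are hard to recover afterwards. If a fuller plan already contains these elements, a sentence in the article saying so would be enough.
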